### 4.3 Life Style Guidelines

Subjects should avoid strenuous exercise during the 24 hours preceding each biosample collection. Walking, moderate cycling and similar activities are allowed.

## 5. STUDY TREATMENTS

### 5.1 Allocation to Treatment

This is an observational study. All patients in this study will receive the standard of care protocol of treatment for their specific malignancy. Healthy subjects will not receive any treatment. Subjects will be enrolled into the study based on whether they are scheduled to receive high dose cisplatin therapy (cisplatin group), non-nephrotoxic therapy (control cancer group) or no treatment (healthy control group).

## **5.2 Drug Supplies**

Standard of care treatment will be provided by the hospital or other institutions where the patients are being treated.

## **5.3 Concomitant Medication**

If any patients require treatment with drugs that are known to be nephrotoxic (e.g. aminoglycoside antibiotics, chronic use NSAIDs) or that interfere with creatinine secretion (e.g. trimethoprim, cimetidine), they will be withdrawn from the study. Any samples collected before they receive any such medications will be included in any pooled analyses of data.

## **5.4 Rescue/Salvage Therapy**

Patients who develop signs or lab test changes that qualify as acute kidney injury will be managed according to the standard protocols of treatment for that institution. This includes both active management and longer-term follow-up of these patients.

The patients' cancer therapy (based on response/non-response to cisplatin for example) will be managed according to that institutions treatment policy for each specific cancer.

# **6. STUDY PROCEDURES**

## **6.1 Screening**

Subjects eligible for the study will have the nature and purpose of the study explained to them by the investigator. They will be provided a written copy of the informed document for the study and given sufficient time to consider the study's implications (e.g. sample collection schedule) before deciding to participate.

The subjects' medical history, prior and concurrent medications, and demographics will be documented. A full physical examination will be done, including blood pressure, body weight and height. A blood sample for BUN and serum creatinine will be taken unless documented by results are available in the previous month. An urine sample will be obtained for routine urinalysis. Eligibility will be determined by checking the inclusion/exclusion criteria.

## **6.2 Study Visits**

### **Cisplatin treatment group**

The cisplatin treatment group of subjects will have blood and urine samples collected as described below. Details of samples collected are given in Section 7.

- Pre-dose blood and urine sample collection before 1st dose of cisplatin chemotherapy.

Patients will then receive the cisplatin infusion as per the standard treatment protocol for their institution. The date and time of starting cisplatin infusion will be recorded in the Case Record Form.

- Blood and urine sample collection within first 12 hours post-1st dose of cisplatin chemotherapy.

Patients who attend for cisplatin treatment on an outpatient basis will have the post-dose set of blood and urine samples collected just before going home. The time of this sample collection will be recorded in the Case Record Form.

For patients who are receiving cisplatin as in-patients, this first post-dose sample should be taken approximately 8 to 12 hours after the start of the cisplatin infusion.

For the 3 weeks following the first cisplatin infusion, patients will attend the clinic on the days described below. Samples should be collected when they arrive in the clinic. If a patient is unable to produce a urine specimen on arrival at the clinic, he/she should be given some fluids to drink in order to produce the sample. As far as possible, clinic visits should be in the morning and should be arranged such that they are within a 2 hour window that is convenient for the patient and clinic staff.

Blood and urine sample collections at:

- 24 hours post-dose.
- 2 days (i.e. 48 hours) post-dose.

Patients should make every effort to attend to give samples at both 24 and 48 hours post-dose. If patients are not able to attend for either time-point, they should be withdrawn from the study and no further samples collected.

- 4 days (+/- 1 day) post-dose.
- 7 days (+/- 1 day) post-dose.
- 14 days (+/- 3 days) post-dose.
- 21 days (+/- 7days) post-dose.

Patients who miss an appointment to give blood and urine samples should be contacted to see if the visit can be rescheduled. If visits cannot be rescheduled and a patient misses more than 2 visits, they should be withdrawn from the study and no further samples collected.

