## **1. INTRODUCTION**

### **1.1 Background and Rationale**

This study is part of a consortium-based clinical programme the aim of which is to develop and qualify novel safety markers of kidney, liver and vascular injury. The SAFE-T consortium is part of the Innovative Medicines Initiative and represents a collaboration between academic institutions, pharmaceutical companies and related small business enterprises, and the European Medicines Agency. The primary aim of this consortium is to develop novel safety markers that can be used both in drug development programmes to monitor organ safety as well as in hospital practice to identify patients at risk of organ injury or detect this injury at an earlier stage and therefore improve the prognosis by prompt intervention and treatment.

Blood urea nitrogen (BUN), serum creatinine and urinary protein (either by dipstick urinalysis or measuring urinary protein/ creatinine ratio) are currently used to monitor renal safety and to detect acute renal injury. Whilst these renal markers are highly specific, at least 50% of renal function may be lost before these markers are able to detect any injury. This can be seen in the case of live donors in renal transplantation where the donor's BUN and creatinine do not usually show any significant change from pre-operative levels. Furthermore, these markers do not usually change until 3 to 5 days after the injury. There is therefore a need for more sensitive markers to detect renal injury at a milder and earlier stage.

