Cisplatin is a widely used and potent chemotherapy drug administered alone or in combination for the treatment of a number of cancers such as testicular, head and neck, ovarian, cervical and non-small cell lung carcinoma, amongst other [Pabla and Dong, 2008]. Its use is limited by adverse effects, notably nephrotoxicity. This occurs in about one-third of patient undergoing high dose cisplatin treatment. Clinically, nephrotoxicity is often seen within about 10 days of cisplatin administration and is manifested as lower glomerular filtration rate, higher serum creatinine, and reduced serum magnesium and potassium levels. It causes proximal and distal convoluted tubular damage by entering tubular cells and activating apoptotic pathways that result in cell death. It also induces the production of TNF, triggering a robust inflammatory response and further contributing to tubular cell injury and death. Cisplatin may also induce injury in the renal vasculature, leading to ischemic tubular cell death and decreased glomerular filtration rate (GFR). Together, these pathological events culminate in acute renal failure in a proportion of patients [Pabla and Dong, 2008].

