### 6.4 Subject Withdrawal

Subjects can withdraw from the study at any time. There will be no study follow up visit and cancer patients will revert to the usual hospital or clinic visit schedule as per their standard of care.

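### Section 6.2 ends all sampling after a missed 24 h or 48 h visit, before the time at which the protocol itself expects creatinine and BUN to show injury

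*Protocol*

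**What the plan says.** Three rules take cisplatin patients out of the study.

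- **Early visits (Section 6.2, Cisplatin treatment group).** On the 24 h and 48 h visits: "If patients are not able to attend for either time-point, they should be withdrawn from the study and no further samples collected".
- **Later visits (same section).** "If visits cannot be rescheduled and a patient misses more than 2 visits, they should be withdrawn from the study and no further samples collected".
- **Drugs (Section 5.3).** Patients who need a nephrotoxic drug are withdrawn, as are those who need drugs "or that interfere with creatinine secretion (e.g. trimethoprim, cimetidine), they will be withdrawn from the study". For this group only, the section adds: "Any samples collected before they receive any such medications will be included in any pooled analyses of data".

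Section 6.4 rules out study follow-up after withdrawal: "There will be no study follow up visit and cancer patients will revert to the usual hospital or clinic visit schedule". Nothing in the protocol provides for retrieving later creatinine values from routine care.

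On timing, Section 1.1 says of BUN, creatinine and urinary protein that "these markers do not usually change until 3 to 5 days after the injury", and of cisplatin that "nephrotoxicity is often seen within about 10 days of cisplatin administration".

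Section 9.2.1 assesses each biomarker on its ability to predict DIKI, defined by AKIN and RIFLE and, separately, by a panel that reviews every cisplatin patient on whatever data are available.

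**The concern.** DIKI is the reference outcome of the study. Sensitivity, specificity, the exploratory ROC curves and the ranking of biomarkers all depend on knowing who developed it. The early-visit rule insists on completeness at two visits where, by the protocol's own account, creatinine is usually still uninformative. It then gives up the visits where creatinine decides the outcome.

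A patient removed this way contributes early biomarker values with no usable outcome. If the reasons for missing a visit are related to how ill the patient is, the patients who remain are not representative, and both DIKI incidence and biomarker performance could be biased. An analysis plan cannot repair this afterwards, because the protocol forbids taking the samples.

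**Working it through.** **1. Early-visit rule against the stated timing.** The scheduled post-dose samples are <12 h, 24 h, 48 h, day 4 (±1), day 7 (±1), day 14 (±3) and day 21 (±7).

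| Reading of *either* | Withdrawn at | Last sample held | Scheduled days lost from day 4 on |
|---|---|---|---|
| One of the two missed, 24 h missed | 24 h | <12 h | 4, 7, 14, 21 |
| One of the two missed, 48 h missed | 48 h | 24 h | 4, 7, 14, 21 |
| Both missed | 48 h | <12 h | 4, 7, 14, 21 |

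Withdrawal falls on day 1 or 2. If injury begins at dosing, the lag ends on days 3 to 5, so withdrawal precedes it by 3 − 2 = 1 to 5 − 1 = 4 days. Later injury widens the gap. The day 4 visit window (4 ± 1, i.e. days 3 to 5) matches the stated lag exactly, and it is the first visit lost.

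**2. Rule for more than two missed visits.** For a patient who attended both early visits, five post-dose visits remain: <12 h, day 4, day 7, day 14 and day 21. The number of ways to miss three of them is C(5,3) = 10.

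| Third miss falls on | Ways | Visits the rule itself forfeits |
|---|---|---|
| Day 7 | 1 (<12 h, day 4, day 7) | Days 14 and 21 |
| Day 14 | 3 | Day 21 |
| Day 21 | 6 | None |

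The rule therefore never acts before the 3 to 5 day lag in these patients. If *either* means both missed, so that one early miss is tolerated, the third miss can come on day 4.

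**3. The two visit rules side by side.** Missing days 4 and 7 counts as two missed visits, which is not more than two, so the patient stays in. Missing one early visit (strict reading) or both (lenient reading) ends participation. Under either reading, the same or a smaller number of misses is penalised more heavily where creatinine tells least.

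**4. Effect on the target of 20 AKI cases.** Section 9.1 plans 100 cisplatin patients to obtain at least 20 with AKI, an implied rate of 20/100 = 20%. It states no rate, probability or withdrawal allowance, so the 100 cannot be strictly reproduced. Section 1.1 gives nephrotoxicity in about one-third of high-dose patients; using that as the AKI rate is an assumption.

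Let p be the AKI rate, w the overall share withdrawn and R the withdrawal risk in AKI relative to non-AKI patients. Then w0 = w / (pR + 1 − p), w1 = R·w0, expected observed AKI = 100·p·(1 − w1), and P is the exact binomial probability of at least 20 with n = 100 and success probability p(1 − w1). All values of w and R are assumptions.

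| p | w | R | Expected observed AKI | Observed rate | P(≥20) |
|---|---|---|---|---|---|
| 1/3 | 0 | – | 33.3 | 33% | 0.999 |
| 1/3 | 20% | 1 | 26.7 | 33% | 0.95 |
| 1/3 | 20% | 2 | 23.3 | 29% | 0.82 |
| 1/3 | 30% | 2 | 18.3 | 26% | 0.37 |
| 20% | 0 | – | 20.0 | 20% | 0.54 |
| 20% | 20% | 1 | 16.0 | 20% | 0.17 |
| 20% | 20% | 2 | 13.3 | 17% | 0.04 |

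Worked line (p = 1/3, w = 20%, R = 2): w0 = 0.20 / (2/3 + 2/3) = 0.15; w1 = 0.30; 100 × 1/3 × 0.70 = 23.3; observed rate 23.3/80 = 29%.

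**The case against.** The best defence is that the study is observational and its comparisons and ROC curves are exploratory, that an early biomarker profile without its 24 h or 48 h sample is of limited use, and that classifying unknown outcomes is ordinarily left to an analysis plan. The first two limit how serious the point is. They do not explain why later samples should be forbidden. The third does not apply to samples that were never taken.

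Several stronger readings are tempting, and the protocol does not support them.

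- *All three rules stop follow-up before injury appears.* Only the early-visit rule does so as a matter of course. The later-visit rule acts mostly on day 14 or 21. The drug rule can act on any day, does not itself say that sampling stops, and has an evident purpose: such drugs confound attribution to cisplatin or distort creatinine.
- *Outcomes are lost selectively.* No passage links missed visits to AKI. Creatinine-defined injury is usually not yet manifest at 24 to 48 h, so renal decline is not an obvious reason for absence; travel or side effects of chemotherapy would serve as well. Selection is possible, not shown.
- *Withdrawn patients are scored DIKI-negative and contaminate the non-cases.* The protocol never says this. The pooling sentence in Section 5.3 covers drug withdrawals only, and pooled analyses may include baseline distributions, where their samples do no harm.
- *The target of 20 cases is undermined.* Section 9.1 allows the cohort size to be adjusted on observed AKI incidence. That answers a shortfall in numbers, though added patients would not remove selection bias if it exists.

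**Conclusion.** The point holds for the early-visit rule. Followed as written, it discards every visit at which the protocol expects creatinine-defined injury to appear, and the protocol has no route to recover the outcome. This follows from the text under both readings of *either* and needs no assumption about rates. The rule for more than two missed visits adds a smaller loss, at most days 14 and 21 for patients who attended both early visits, and the two visit rules do not fit together.

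The number of patients affected is unknown, and any bias in incidence or biomarker performance cannot be sized from the protocol. The case-count figures are illustrative only. At one-third the target survives a 20% non-selective loss and fails only if loss is both large and selective. At 20% it is close to an even chance (0.54) before any withdrawal, so a shortfall there could not be put down to these rules alone.

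**What to change.** - **Section 6.2:** replace withdrawal for missed visits with an instruction to record the missed sample as missing and continue all later scheduled samples, including creatinine and BUN, through Day 21 for patients who remain willing. If any early-visit condition is kept, say whether *either* means one visit or both.
- **Section 9.2.1:** state that patients without outcome follow-up have DIKI status unknown and are not counted as DIKI-negative.
- **Sections 5.3 and 9.2.1:** leave the drug-withdrawal rule in place, but reconcile the two sections on how DIKI status is set for these patients. Creatinine measured after a creatinine-altering drug should not by itself define DIKI.

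The cost is a wording amendment. The visits and samples are already scheduled. The downside is some incomplete biomarker profiles, which the time-course endpoints in Section 2.2 will have to accommodate.

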### **Control groups**

Control subjects (non-cisplatin treated cancer patients, healthy volunteers) will have blood and urine samples collected as described below. Note that for cancer control group patients who are receiving inpatient treatment, morning blood and urine will be collected in the hospital or clinic they are being treated in. Details of samples collected are given in Section 7.

Blood samples and a urine sample will be collected when subjects arrive in the clinic. If a subject is unable to produce a urine specimen on arrival at the clinic, he/she should be given some fluids to drink in order to produce the sample. As far as possible, clinic visits should be in the morning and should be arranged such that they are within a 2 hour window that is convenient for the patient and clinic staff.

Samples should be provided on:

- Visit 1: this should be within 3 weeks of the Screening assessment (see previous regarding combining Screening and Visit 1).
- Visit 2: this should 2 days (+/- 1 day) after Visit 1.

### 6.3 Follow-up Visit

Since this is an observational study, there will be no follow up visit. Cancer patients (both cisplatin-treated group and control patients) will be followed up and treated according to the standard of care protocol of their hospital or institution. The investigator should check that patients have an appointment for their next cancer treatment or clinic visit as appropriate.

### 6.4 Subject Withdrawal

Subjects can withdraw from the study at any time. There will be no study follow up visit and cancer patients will revert to the usual hospital or clinic visit schedule as per their standard of care.

## 7. SAMPLE COLLECTION & HANDLING

10 mL blood (serum) and 40 mL urine samples will be collected at each visit for the following kidney biomarkers:

**Table 3:** Novel biomarkers to be measured in this study

| Type of biomarker                    | Biomarker name*                                      | Main significance                                                                                                                               |
|--------------------------------------|------------------------------------------------------|-------------------------------------------------------------------------------------------------------------------------------------------------|
| Functional biomarkers         | Microalbumin/Albumin                                 | Marker of impaired proximal tubular reabsorption                                                                                                |
|                                      | $\alpha$ -1 microglobulin                            | Marker of impaired proximal tubular reabsorption and indirectly of glomerular injury                                                            |
|                                      | Cystatin C                                           | Evaluation of glomerular filtration rate (serum)
Marker of impaired proximal tubular reabsorption and indirectly of glomerular injury(urine) |
|                                      | Urinary creatinine                                   | Marker of impaired proximal tubular reabsorption and indirectly of glomerular injury(urine)                                                     |
|                                      | Retinol Binding Protein-4 (RBP-4)                    | Marker of impaired proximal tubular reabsorption                                                                                                |
| Tissue injury leakage markers | N-acetyl- $\beta$ -D-glucosaminidase (NAG)           | Marker of proximal tubular injury                                                                                                               |
|                                      | Glutathione-S-transferase- $\alpha$ (GST- $\alpha$ ) | Marker of proximal tubular injury                                                                                                               |
|                                      | Glutathione-S-transferase- $\pi$ (GST- $\pi$ )       | Marker of distal tubular injury                                                                                                                 |
|                                      | Liver-type fatty acid binding protein (L-FABP)       | Marker of proximal tubular injury                                                                                                               |
|                                      | Collagen IV                                          | Marker of glomerular injury                                                                                                                     |
|                                      | Podocin                                              | Marker of glomerular injury                                                                                                                     |
|                                      | Nephrin                                              | Marker of glomerular injury                                                                                                                     |
|                                      | Aquaporin-2                                          | Marker of collecting duct injury                                                                                                                |
| Tissue injury response        | Calbindin D28                                        | Marker of injury to distal regions of nephron and collecting ducts                                                                              |
|                                      | Kidney injury molecule-1                             | Marker of proximal tubular                                                                                                                      |

| Type of biomarker | Biomarker name*                                   | Main significance                                                                   |
|-------------------|---------------------------------------------------|-------------------------------------------------------------------------------------|
| markers           | (KIM-1)                                           | injury/regeneration                                                                 |
|                   | Clusterin                                         | Marker of tubular injury/regeneration (no apparent specific nephronal localization) |
|                   | Neutrophil gelatinase associated lipocalin (NGAL) | Marker of tubular (mainly proximal) injury                                          |
|                   | Trefoil Factor 3 (TFF3)                           | Marker of proximal tubular injury                                                   |
|                   | Osteopontin                                       | Marker of injury to distal regions of nephron                                       |
|                   | Tissue inhibitor of metalloproteinase-1 (TIMP-1)  | Marker of interstitial fibrosis and tubular injury                                  |
|                   | Connective Tissue Growth Factor (CTGF)            | Marker of interstitial fibrosis                                                     |
|                   | Interleukin-18 (IL-18)                            | Marker of inflammation                                                              |
|                   | Monocyte chemoattractant protein-1 (MCP-1)        | Marker of inflammation                                                              |

\* All biomarkers will be assessed in urine and Cystatin C and NGAL will additionally be assessed in plasma/serum.

A 10 mL EDTA blood sample will be taken at the baseline and Day 7 visits only. The plasma obtained from these samples will be stored for future use for novel renal and other organ safety biomarkers.

Additional the following parameters will be assessed in the 5 ml blood plus 10 ml urine for routine diagnostics.

|                 |                                                                                                        |
|-----------------|--------------------------------------------------------------------------------------------------------|
| Blood Chemistry | Total protein, Albumin, Creatinine, Urea
Sodium, Chloride, Calcium, Phosphate, Potassium, Magnesium |
| Urinalysis      | U-Kreat; U-Urea; Na, K, U-Protein, U-Albumin (Midstream)                                               |

**Table 4:** Type of Samples and Approximate Amount of Blood and Urine to be collected from Each Subject

| Test                      | Sample volume (mL) | Number of visits sampled |                | Total volume (mL) |                |
|---------------------------|--------------------|--------------------------|----------------|-------------------|----------------|
|                           |                    | Cisplatin group          | Control groups | Cisplatin group   | Control groups |
| Routine laboratory test   | 5                  | 9                        | 3              | 45                | 15             |
| DIKI serum sample         | 10                 | 8                        | 2              | 80                | 20             |
| DIKI EDTA blood           | 10                 | 2                        | 2              | 20                | 20             |
| Total blood volume | -                  | -                        | -              | 145        | 55      |
| Routine urinalysis        | 10                 | 9                        | 3              | 90                | 30             |
| DIKI urine sample         | 40                 | 8                        | 2              | 320               | 80             |
| Total urine volume | -                  | -                        | -              | 410        | 110     |

